## Abstract

**Background:**

Up to 50% of kidney transplant patients are diagnosed with delayed graft function (DGF) following transplantation—the majority being linked to ischaemia reperfusion injury (IRI). DGF is traditionally defined as the requirement for dialysis during the first week after transplantation and is associated with inferior graft and patient outcomes. Local synthesis of complement components, largely by the renal tubule, plays a critical role in IRI. We have developed Mirococept, a membrane-targeted complement inhibitor, that can be administered to the donor kidney ex vivo prior to transplantation. After administration, Mirococept is retained in the donor organ, thereby minimising the risk of systemic side effects. We previously launched the EMPIRIKAL study aiming to evaluate the efficacy of Mirococept in reducing DGF in deceased-donor kidney transplantation (KT). The funding body recommended termination of the study to allow a dose-saturating study before the next stage of clinical evaluation. This was carried out in a porcine kidney model and led to a revised dosing regimen for EMPIRIKAL-2 (60–180 mg compared with 5–25 mg in the initial trial). The EMPIRIKAL-2 trial (REC 24/NE/0071) aims to identify the most safe and efficacious dose of Mirococept to reduce DGF rate in deceased-donor KT.

**Methods and analysis:**

EMPIRIKAL-2 is a Phase IIa multicentre double-blind randomised controlled trial (RCT) with an initial safety run. Participants will be recruited from renal departments at National Health Service tertiary hospital sites in the UK. The purpose of the safety run is to assess the tolerance of each of the three proposed Mirococept doses (60, 120 or 180 mg), before the RCT begins. Three patients will be assigned to each treatment dose, starting from the lower dose. The safety run will be considered successful if at least one dose can be taken forward to the RCT for comparison to placebo.

If safety is met, 144 participants (36 per arm excluding drop-outs) will be randomised to all doses meeting the safety criteria or placebo on a 1:1:1:1 basis. The primary endpoint is DGF, defined as the requirement for dialysis during the first week after transplantation. Safety evaluation will include the monitoring of laboratory data and the recording of all adverse events. Immunosuppression therapy, antibiotic and antiviral prophylaxis will be administered as per local centre protocols. Enrolment in the RCT is anticipated to take approximately 12 months, and patients will be followed-up for 12 months.

**Ethics and dissemination:**

The study has been approved by the Northeast - Newcastle and North Tyneside 2 Research Ethics Service Committee, REC reference 24/NE/0071. The results of the study will be reported and disseminated at international conferences and in peer-reviewed scientific journals. Once published, a lay summary of the results will be made available to participants who request this information.

**Trial registration number:**

ISRCTN14279222. Registered on 4 July 2024.

**Protocol version:**

2.0 dated 9 May 2024.

STRENGTHS AND LIMITATIONS OF THIS STUDYThis is a multicentre, multi-arm, double-blind randomised placebo-controlled dose-finding trial with an initial safety run.The initial safety run will establish the best tolerated dose of Mirococept which will be taken forward to the randomised controlled trial for comparison to placebo.Mirococept, given by ex vivo administration, is retained in the donor kidney, thus minimising the risk of systemic side effects.The study is powered to detect a reduction of delayed graft function from 50% down to 30%, which may not apply to other centres where there is a different case mix.

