### Multi-arm randomised placebo-controlled trial

If all three doses are found to be safe and well tolerated in the safety run, 144 participants (36 per arm) will be randomised to receive a kidney perfused with Mirococept or placebo on a 1:1:1:1 basis, stratified by centre and donor type. 90 participants (30 per arm) will be required if two of the proposed doses are well-tolerated, and 40 participants (20 per arm) will be randomised if only one dose can be taken forward for comparison with placebo.

The participants enrolled in the safety run will not be included in the RCT analysis.

The primary outcome of DGF will be assessed at seven completed days post-transplantation, and participants will be followed-up for 12 months. The design will be a double-blind, randomised placebo-controlled trial and will therefore minimise bias.

Safety assessments during this randomisation stage will include routine renal function and urine tests, with further investigation (eg, renal ultrasound and Doppler) as appropriate and complement activity and serum Mirococept levels as per trial protocol.

In the event that DGF rate and safety outcomes are similar in more than one dosing group, the final decision on which dose to take forward to the next clinical trial will include the secondary outcome measures. Of these, the most important are: functional DGF rate (where the fall in creatinine is less than 10% per day for three consecutive days); and AUC (area under the curve) based on the drop-in serum creatinine level in the first 2 weeks after transplantation where the participant does not require postoperative dialysis. If the combined primary and secondary endpoints of efficacy and the safety outcomes do not discriminate between the two doses, then the lower of the two doses would be taken forward to the next trial.

If this trial is successful and subject to funding being secured, the best dose will be taken forward into a definitive two-arm trial against placebo. The experimental unit, follow-up time points, randomisation and blinding will be the same in this second stage of the adaptive design.

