## Statistics

EMPIRIKAL-2 is an operationally seamless adaptive design to evaluate safety and superiority of Mirococept in reducing DGF in deceased donor kidney transplantation, as compared with placebo. The trial is randomised, double blind and placebo controlled to minimise bias.

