### Sample size

Nine patients will be needed for the safety run. Allowing for a 10% drop-out rate, the target sample size will be 10 patients for this stage.

For the main multi-arm randomised placebo-controlled stage, the required sample size was calculated using a selection theory approach as proposed by Simon *et al*.^26^ Software from the Centre for Clinical Research and Biostatistics, Hong Kong was used: (https://www2.ccrb.cuhk.edu.hk/stat/phase2/Randomized.htm).

The parameters for this calculation are p=0.30, D=0.20 and k=4, where p is the estimated percentage of the lowest response rate among all treatments, D is the difference in response rate between the best dose of Mirococept and all the other treatment groups including placebo, and k is the number of treatment arms.

A sample size of 144 (36 in each arm) will be required to correctly identify the best dose of Mirococept with 90% probability. 30 patients per arm will be required if two of the proposed doses are well-tolerated and 20 patients per arm if only one dose is well-tolerated in the safety run. Allowing for a 10% drop-out rate, the target sample size for a 4-arm study will be 160 participants (40 in each arm).

Overall, up to 170 participants are needed for the safety component and main randomised study.

A sample size of 40 per arm will produce a two-sided 95% CI for the difference in population proportions with a precision that is equal to ±21.1% when the estimated DGF rate in the treatment arm is 30% (vs 50% in placebo).

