### Analysis

Analysis will occur at the end of the trial comparing differences in DGF proportions between each dose and the control along with CIs. Safety assessments during the randomisation stage will include routine renal function and urine tests, with further investigation (eg, renal ultrasound and Doppler) as appropriate and complement activity and Mirococept levels as per the current protocol.

In the event that DGF rate and safety outcomes are similar in more than one dosing group, the final decision on which dose to take forward to the pivotal Phase III clinical trial will include the secondary outcome measures. Of these, the most important are: functional DGF rate (where the fall in creatinine is less than 10% per day for three consecutive days); and AUC based on the drop in serum creatinine level in the first 2 weeks after transplantation where the patient does not require postoperative dialysis. If the combined primary and secondary endpoints of efficacy and the safety outcomes do not discriminate between two doses, then the lower of the two doses would be taken forward to the next trial.

This would be a confirmatory Phase III trial (to be separately funded) with two arms—the best-selected dose from the current trial vs the placebo control—each of which requiring 124 patients. Differences in DGF rates would be compared between the treatment and control arms using logistic regression adjusting for stratification factors.

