### Effect size

Reduction in DGF from 50% to 30% (ie, a 20-point reduction; 40% relative reduction), control versus treatment, is predicted. The base rate of 50% is modelled on Guy’s Hospital audit data over the past 3 years and consistent with DGF rates of 60% and 40% reported for DCD and DBD, respectively, in a Cambridge study of 525 consecutive kidney transplants.^27^ The estimated 20%-point reduction is justified by a life-sustaining rat isograft model in which the frequency of non-functioning grafts was reduced from 73.3% in the control arm to 36.4% in the treatment arm.^20^ Rat donor kidneys with IGF had more rapid recovery than controls, with a relative reduction in AUC of creatinine during week 1,^20^ justifying use of this measure as a secondary endpoint in the trial. A clinical trial of ex vivo normothermic perfusion in DCD kidneys was powered for a 15%-point reduction in DGF (from 50% to 35%; a 30% relative change) with power of 80% and statistical significance of α=0.05, that is, within range of the predicted effect size.^28^

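### The article says the trial is powered to detect a fall in DGF from 50% to 30%, but its sample size secures only a 90% chance of ranking the best arm first; power against placebo is about 41%, 35% or 25% at 36, 30 or 20 per arm

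*Protocol article*

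**What the plan says.** Two places describe the trial as if it were sized for a test against placebo. The strengths and limitations box says "The study is powered to detect a reduction of delayed graft function from 50% down to 30"%. The Statistics section says the design is "to evaluate safety and superiority of Mirococept in reducing DGF", and Methods/design says much the same.

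The Sample size section gives a different basis: "the required sample size was calculated using a selection theory approach". "The parameters for this calculation are p=0.30, D=0.20 and k=4", where D separates the best dose from every other group, placebo included. The stated result is "A sample size of 144 (36 in each arm) will be required to correctly identify the best dose of Mirococept with 90% probability". With two tolerated doses the figure is 30 per arm. With one, "40 participants (20 per arm) will be randomised if only one dose can be taken forward for comparison with placebo". The same section gives a two-sided 95% interval half-width of ±21.1 points at 40 per arm for 30% against 50%.

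The Effect size section sets the contrast: "Reduction in DGF from 50% to 30% (ie, a 20-point reduction; 40% relative reduction), control versus treatment, is predicted". The Analysis section plans differences between each dose and control with confidence intervals, and describes a later two-arm Phase III trial with arms "each of which requiring 124 patients".

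**The concern.** A selection design answers one question: if one arm is better than the rest by a given margin, how often will it come out on top? It sets no type I error rate and gives no power for a comparison with placebo. Some arm always ranks first. Calling such a trial powered to detect a 20-point fall presents a 90% probability of correct ranking as a property of a test.

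What is at stake is how the result is read. Someone who relies on the power statement could take an interval that includes zero as evidence against Mirococept, although under the assumptions below that is the more likely outcome at the planned effect. The same reader could take the top-ranked dose as shown superior to placebo.

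**Working it through.** **Inputs.** DGF 50% on placebo and 30% on treatment (Effect size). 36, 30 or 20 evaluable per arm; p = 0.30, D = 0.20; 40 per arm before drop-out (Sample size). No alpha is stated for this trial; the α = 0.05 in Effect size belongs to another trial. *Assumption:* two-sided 5%, to match the 95% interval; one-sided 5% is shown as a range.

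**1. The plan's own figures.** Exact binomial probability that the best arm (p + D = 0.50) ranks first against k − 1 arms at 0.30, ties broken at random:

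| Arms (k) | n per arm | P(correct ranking) | at n − 1 |
|---|---|---|---|
| 4 | 36 | 0.903 | 0.898 |
| 3 | 30 | 0.903 | 0.898 |
| 2 | 20 | 0.903 | 0.897 |

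All three are the smallest n that reaches 90%, so the sizes are right for selection. The drop-out step also reproduces: 36 / 0.9 = 40.

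**2. Power for the claimed contrast.** With pooled rate 0.40,

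power ≈ Φ{[0.20·√n − z·√(2 × 0.40 × 0.60)] / √(0.50 × 0.50 + 0.30 × 0.70)} = Φ{[0.20·√n − z × 0.6928] / 0.6782}

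At n = 36, z = 1.96: [1.200 − 1.358] / 0.6782 = −0.233, so Φ = 0.408.

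| n per arm | Formula, two-sided 5% | Exact chi-square, two-sided 5% | Formula, one-sided 5% |
|---|---|---|---|
| 36 | 40.8% | 41.0% | 53.5% |
| 30 | 34.9% | 35.1% | 47.4% |
| 20 | 24.7% | 24.5% | 35.9% |

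Exact enumeration of the one-sided test at 36 per arm gives 57.1%, hence the range 54–57%. With no drop-out (40 per arm) the two-sided figure is 44.6% by formula and 45.8% exactly. Fisher's exact test is lower: 30.9% at 36 and 16.3% at 20.

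**3. Size needed.** n = [1.96 × 0.6928 + z_β × 0.6782]² / 0.20². For 80% power (z_β = 0.842) this is 93 per arm. For 90% power (z_β = 1.282) it is 124 per arm, the same as the figure given for the later Phase III trial.

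**4. Precision.** Half-width = 1.96 × √[(0.25 + 0.21)/n]:

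- n = 40: 21.0 points (stated 21.1; the difference is trivial)
- n = 36: 22.2 points
- n = 20: 29.7 points

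Each exceeds 20 points, so an interval centred on the predicted effect includes zero.

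**The case against.** The best defence is that the Sample size section is correct and open. It names the method, its parameters and its 90% criterion, claims no test, and prints the interval half-width that shows the imprecision. The Analysis section plans estimates with intervals and leaves confirmation to Phase III. All of that stands, and it confines the fault to one summary statement and the word superiority. It does not rescue the statement: an affirmative claim of power in the published text cannot be made true by an analysis plan not shown here.

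Four stronger readings are tempting, and the documents do not support them.

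- *With one dose left there is nothing to select, so 20 per arm has no rationale.* The Sample size section counts placebo as an arm in both D and k. With k = 2 the procedure ranks dose against placebo, and 20 per arm still ranks them correctly 90% of the time.
- *The 124 per arm is an outright contradiction.* It matches 90% power for 50% against 30% at two-sided 5%, but the article does not state the inputs. A confirmatory trial may also properly be larger than a Phase IIa selection trial. The match is supporting evidence only.
- *A useless dose would probably go forward.* That needs a rule that any numerical advantage over placebo counts as success. The protocol contains no such rule and does not define success numerically.
- *Power should be cut further for three comparisons.* The protocol proposes no multiplicity-adjusted test, so no such figure is used here.

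**Conclusion.** The concern holds as a misstatement of what the sample size delivers. For a fall from 50% to 30%, the trial has about 41%, 35% or 25% power against placebo at 36, 30 or 20 per arm. At 36 per arm and the planned effect, a test would miss it about 59% of the time (1 − 0.41). These figures rest on an assumed two-sided 5% level. One-sided 5% raises the first to 54–57%, still well short of the usual 80%, so the conclusion does not depend on the choice.

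Nothing here shows that the sample size is wrong for its stated selection purpose, or that more patients are needed.

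**What to change.** 1. Replace the power sentence in the strengths and limitations box with: *The trial is sized to rank the best arm first with 90% probability if it is 20 points better than every other arm including placebo; it is not powered to test superiority over placebo (about 41%, 35% or 25% power at 36, 30 or 20 per arm, two-sided 5%).* The caution about case mix at other centres can stay.
2. In Methods/design and in Statistics, replace superiority with dose selection and estimation against placebo.
3. In Sample size, add that with one tolerated dose, 20 per arm gives a 90% probability of ranking dose and placebo correctly but only an imprecise estimate of the difference, about ±30 points.

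The cost is wording only. The stated figure becomes less favourable; the design, the arm sizes and the number of patients do not change.

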## Background

### DGF in kidney transplant patients

 Up to 50% of kidney transplant patients are diagnosed with delayed graft function (DGF) following transplantation—the majority being linked to ischaemia reperfusion injury (IRI). DGF has traditionally been defined as the requirement for dialysis within the first week after transplantation, although over 10 definitions have been recorded in the literature.^1^ The incidence of DGF has risen substantially over the last decade due to a marked increase in the use of donation after circulatory death (DCD) and expanded criteria donor (ECD) kidneys.^2 3^ DGF is associated with higher rates of acute rejection, reduced kidney transplant survival and prolonged hospitalisation.^4 5^ The relative risk of graft loss and death at 5 years in patients with DGF is 1.89 and 1.64, respectively.^6^ Strategies to prevent IRI and consequent DGF are therefore more relevant today than 10 years ago.

### Role of complement in IRI

The complement system plays a critical role in all forms of solid organ IRI.^7^ The reperfusion of the ischaemic kidney induces a proinflammatory reaction in which the complement system activation plays a central role.^8^ Complement-depleted or deficient animals exhibit reduced post-ischaemic acute renal failure and chronic nephropathy.^9^,^11^ The evidence strongly suggests that local synthesis of complement components largely by the renal tubule has a prominent role in activating local inflammatory processes and mediating graft immunogenicity, more so than the circulating pool produced by hepatic synthesis.^9^ The central step in complement activation is the cleavage of C3 to C3b by C3 convertase. Membrane-bound C3b binds to activated factor B and forms the C3 convertase enzyme resulting in further C3 cleavage to C3b. This ultimately leads to C5a and C5b-9-mediated injury of the renal tubule, and C3a and C5a-mediated enhancement of the recipient immune response.^12 13^ In vivo, the aberrant complement activation is prevented by the regulators of complement activation (RCAs). RCAs are poorly expressed on the tubule surface both in normal and ischaemic kidneys, making the tubule vulnerable to complement attack.

Together, these mechanisms provide a rationale for local therapeutic manipulation of C3 function during early transplantation in order to improve the short and possibly longer-term outcomes of renal grafts. Such a targeted approach would provide graft protection while avoiding the off-target effects of systemic complement inhibition in immunosuppressed recipients.

### Regulators of complement activation and therapeutic potential

Mirococept (APT070) is a highly effective complement inhibitor which is derived from CR1 (CD35). It consists of three functional units: the terminal three short consensus repeat domains of CR1 which contain its biological activities, a membrane associating peptide and a membrane-inserting myristoyl group.^14^ The last two units permit the binding to and insertion into the cell membrane. Mirococept is unique in that it is engineered to bind to cell surfaces in bulk^15^ and can block the complement system at the C3 level. It does not inhibit proteases generally, and its action is restricted to the complement system.

Mirococept’s selectivity derives from the extensive contact surface between the complement control protein domains of the CR1 fragment and C3b, which is a component of the alternative and classical pathway-derived C3 and C5 convertases. Mirococept inhibits these convertases by two highly specific mechanisms, one by inducing dissociation of the subunits of the convertases and the other by acting as a cofactor for the proteolytic breakdown of C3b by the endogenous serum protease factor I.

### Preclinical studies

Mirococept has undergone proof-of-concept evaluation in animal models of inflammation including rheumatoid arthritis,^16^ Guillain-Barré syndrome,^17^ intestinal ischaemia^18^ and myocardial ischaemia.^19^ We previously developed a strategy to administer Mirococept in the donor kidney, thereby avoiding any undesirable consequences from systemic complement inhibition.^10^ After being administered to the kidney ex vivo via the renal artery, Mirococept localises to the graft endothelial and epithelial cells. In a rat transplant model with 30 min of cold ischaemia, we showed that local inhibition of complement activation within the graft by Mirococept reduced complement-mediated injury and lowered the ability of the kidney to initiate acute cell-mediated rejection.^10^ Specifically, Mirococept reduced inflammatory injury and allograft rejection, thus improving graft function in the short term (throughout the first week) and long term (20 weeks). With prolonged cold ischaemia (16 hours), treatment led to reduced complement deposition and inflammation in transplanted kidney, with graft losses reduced to 36.4%, compared with 73.3% in control-treated organs. Moreover, the treated rat kidneys that remained viable after transplantation had a more rapid rate of recovery than controls, with 33% relative reduction in area under the curve (AUC) of creatinine over the first 7 days.^20^

### Clinical studies

A summary of the clinical studies of Mirococept can be found in table 1.

**Table 1 T1:** Summary of clinical studies of Mirococept to date

Study	Cohort	Dose	Outcomes
Phase I	42 healthy human volunteers	2–100 mg intravenous	Good tolerability at doses up to 100 mg
Phase IIa pilot	16 kidney transplant patients	10 mg	Trend towards faster recovery in IGF group
Phase II (EMPIRIKAL)	First cohort of 80 kidney transplant patients	10 mg	Trend towards faster recovery in IGF group

IGFimmediate graft function

A Phase I study in human volunteers treated with incremental doses (2–100 mg) of intravenous Mirococept showed a favourable safety profile (see Safety below).

A Phase IIa pilot study in 16 kidney transplant patients confirmed the feasibility of the ex vivo administration of Mirococept at 10 mg/kidney prior to transplantation and showed a trend towards more rapid recovery of graft function compared with control organs.^21^

The first EMPIRIKAL Phase II study set out to evaluate the dose and efficacy of Mirococept in reducing DGF rates in deceased donor kidney transplantation.^22^ The design was to test a dose range of 5–25 mg in cohorts of 80 patients for each dose with a maximum number of seven cohorts. This dose range was scaled up from data in a rat transplant model in which renal functional recovery was the principal measure of efficacy.^10 20^ The results with the first dose (10 mg, infused into the donor organ), however, showed no effect on DGF rate compared with the control group (although there was an encouraging trend towards faster recovery of renal function associated with Mirococept in patients with immediate graft function (IGF). The funding body—the Medical Research Council, UK—recommended termination of the study to allow a dose-saturating study before the next stage of clinical evaluation.

